#### tDCS device

The tDCS treatment will be applied using a battery-driven, portable tDCS device (Neurophet innk; Neurophet) and two sponge-coated 5 × 5 cm^2^ electrodes. The stimulation parameters will be set using the bundled software. The parameters in Group A will be as follows: tDCS mode, current intensity of 2 mA, and simulation time of 30 min. In Group B (sham tDCS), the sham mode of the software will be used; the stimulation time will be the same as in Group A, while the current will be increased to 2 mA over the first 30 s and then decreased to 0 mA over the next 30 s (15). The current will then be maintained at 0 mA for the next 28 min, increased to 2 mA over 30 s, and finally decreased to 0 mA over the next 30 s.

The tDCS device can check impedance in real time. If the impedance is >13 kOhm, the stimulation will be stopped and the IDM will check the condition of the patient’s skin to prevent adverse events.

Each tDCS intervention will be performed 10 times over 2 weeks. Then, the other tDCS intervention will be performed depending on the group assignment. Any rehabilitation programs in which the participants are enrolled can be continued during the study. The electrode locations will be the same in the sham tDCS and P-tDCS groups.

#### P-tDCS

The P-tDCS process consisted of four steps: MRI segmentation, 3D brain modeling, personalized tDCS planning based on the simulation of E-field, and the treatment. The whole process is going to be conducted using NEUROPHET tES LAB. All participants undergo baseline MRI scans before enrollment. On MRI scans, if a skull bone defect (such as a burr hole) is detected in patients with a history of surgery, or if an implant such as a cable or coils is found, the principal investigator will discuss it with a neurology and neurosurgery specialist to decide whether the patient can participate in the study. After confirming that, as the first step for planning tDCS, the MR image segmentation will be semi-automatically labeled into eight layers: skin, skull, cerebral and cerebellar white matter, gray matter, cerebrospinal fluid, and affected tissue (14). If a patient has a pre-existing implant, their MRI will be segmented manually based on computed tomography scans and X-rays. The second process is brain modeling. Based on the labeled images and segmented data, a 3D model of tetrahedron meshes is generated. Third, P-tDCS planning is based on the simulation of the E-field. The tDCS-induced E-field in the 3D head and brain model is computationally simulated based on the finite element method (FEM). For computational simulation, the electrical conductivity was assigned to a head and brain tissue; scalp = 0.465, skull = 0.01 CSF = 1.65, ventricle = 1.65, white matter = 0.126, gray matter = 0.276, affected tissue = 0.8087, all in S/m (16) To plan P-tDCS in NEUROPHET tES LAB, the Left DLPFC is localized according to a widely used method, in which F3 on the 10–20 electroencephalogram (EEG) system is selected as the anode placement site (center of anode electrode over F3). The method for the P-tDCS plan is a built-in tES LAB feature to determine the optimized position of an anode electrode among several candidate positions around F3, based on the E-field of the Lt DLPFC region.

### Outcomes

K-CRS-R: The CRS is a neurobehavioral assessment instrument used to evaluate the state of consciousness of patients with severe brain injury; it is able to predict the treatment outcome with high accuracy. The CRS-R was released in 2004 and reflects the diagnostic criteria for MCS developed by the Aspen Workgroup in 2002 (2); it is the most effective tool for assessing long-term DOC patients and is recommended by the American Congress of Rehabilitation Medicine (17). The CRS-R distinguishes MCS from *VS* based on six sub-domains (auditory, visual, motor, oral movement/language, communication, and arousal). Total scores range from 0 to 23; higher scores indicate a higher level of function. The validity of the K-CRS-R was established through comparison with the CRS-R (18).

EEG: EEG is a reliable, non-invasive modality to examine the state of consciousness of patients with DOC (18). The spectral power, complexity, and functional connectivity of the theta and alpha bands are related to the state of consciousness, and combining behavioral measures with and EEG is optimal for evaluating the possibility of improving a patient’s consciousness. Brain function changes after tDCS will be evaluated in this study *via* power spectral analysis of the brain region of interest. Interactions and connectivity will be evaluated based on the correlations of EEG phase and amplitude (19, 20).

Functional magnetic resonance imaging (fMRI): fMRI can reveal blood flow changes in response to brain activation by various stimuli. An increase in activity in the brain region associated with mental imagery in a patient with a consciousness disorder imagining performing a specific task indicates that the task instructions are being followed. Because it will be difficult to perform fMRI as a routine examination due to the characteristics of the patients in this clinical trial, it will only be used where available as an exploratory analysis.

Fluorodeoxyglucose-positron emission tomography (FDG-PET): PET measures the activity in a brain area within a short period of time. Hypometabolism is particularly severe in the bilateral frontoparietal cortex of patients with long-term unconsciousness, and metabolic recovery in this area is correlated with the recovery of consciousness (21). In this clinical trial, FDG-PET will be conducted only when it is judged as feasible by the investigator and is thus considered as an exploratory endpoint.

Nociception Coma Scale-Revised (NCS-R): The NCS is used to detect pain in patients with impaired consciousness (22, 23). It consists of four subscales that evaluate facial expressions and motor, verbal, and visual responses to noxious stimuli; total scores range from 0 to 12 points. The NCS-R only evaluates motor, verbal, and facial responses, and total scores thus range from 0 to 9 points (24).

#### Primary and secondary outcomes

The primary outcome will be the change in total K-CRS-R score 2 weeks after the baseline assessment. The secondary outcomes will be changes in the total K-CRS-R score after 1 and 2 weeks, and at the end of the study. Score changes in the auditory, visual, motor, oral motor/linguistic function, communication, and arousal domains will be assessed, along with changes in EEG activity. The exploratory endpoints are fMRI and FDG-PET changes after 2 weeks. The safety endpoints are the NCS-R score, vital signs, and concomitant drug use.

### Sample size estimates

The purpose of this study is to validate the feasibility of P-tDCS for consciousness recovery in patients with PDOC. The effect size f of P-tDCS is expected to be at least 0.25 and the power 0.80, so this study should enroll 22 participants, assuming a drop-out rate of 10%, a total of 24 participants will be enrolled, which is G-Power (version 3.1.9.7) software was used to calculate. The sample size is larger than a previous study of MCS patients (9) and is considered as an appropriate basis for pivotal trial design (25).

### Statistical analyses

As stated above, the primary outcome is the change in total K-CRS-R score 2 weeks after the baseline assessment. Repeated-measures analysis of covariance (ANCOVA) will be performed to compare the groups, with the baseline K-CRS-R score included as a covariate. The first secondary outcome to be evaluated will be the change in total K-CRS-R score 1 week after the baseline assessment and at the end of the study. Repeated-measures ANCOVA will be performed to compare the groups, with the baseline K-CRS-R score included as a covariate. The second secondary outcome will be the changes in K-CRS-R subscale scores at 1 week, 2 weeks, and the end of the study compared to the baseline. Repeated-measures ANCOVA will be performed to compare the groups, with the baseline K-CRS-R score included as a covariate. The third secondary outcome will be the changes in EEG 2 weeks after the baseline assessment and at the end of the study. Repeated measures ANCOVA will be performed, with the baseline EEG results included as a covariate. Finally, repeated-measures analysis of variance will be performed to compare the groups at each time point in terms of changes in fMRI and FDG-PET results relative to baseline. Descriptive statistics (mean ± standard deviation and median and range) will be generated for each outcome. A *p*-value <0.05 will be considered significant.

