### Enrollment and randomization

Participants will be assigned a random number at baseline and randomized to either Group A or Group B. As this trial uses a cross-over design, the only difference between the two groups is the order of the intervention [Group A: P-tDCS (period 1), washout period (> 2 weeks), and sham tDCS (period 2); Group B: sham tDCS (period 1), washout period, P-tDCS (period 2)].

All participants will be randomly assigned to the groups at a 1:1 ratio according to the order of registration by the investigator. The statistician for this clinical trial will use the latest version of SAS statistical software (SAS Institute, Cary, NC, USA) to issue random numbers. A stratified block randomization method will be used with a predefined block size; institution will be a stratification factor. Envelopes containing the study numbers will be provided to the “investigational device manager” (IDM) before the participants are registered.

To maintain blinding of the IDM, an unblinded investigator will be assigned to each institution, and will provide the participants with devices according to their group assignments. The unblinded investigators will not participate further in the study.

This parallel randomized controlled trial uses a cross-over design given the clinical needs of the DOC patients. There is no gold standard treatment for DOC, although tDCS may be useful. However, use of tDCS is prohibited in Korea, except in clinical trials, and the treatment options for DOC patients are limited. Benefits of tDCS have been reported in some cases of DOC (13). Because sham group patients would not receive any of the benefits of tDCS due to the parallel study design, a cross-over design is used so that all participants will have the same opportunity to receive tDCS.

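### End-of-study comparisons of Group A with Group B contrast treatment orders and do not estimate P-tDCS versus sham; the 2-week primary is valid but uses period 1 only and falls well short of the stated power

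*Protocol article*

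**What the plan says.** Enrollment and randomization describes a two-period cross-over with 1:1 allocation. Group A receives P-tDCS then sham, Group B the reverse, and "the only difference between the two groups is the order of the intervention". The section on the tDCS device uses the same letters as treatment labels. It gives the active settings as those of Group A and says "In Group B (sham tDCS), the sham mode of the software will be used". That is true in period 1 only.

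In Statistical analyses, "the primary outcome is the change in total K-CRS-R score 2 weeks after the baseline assessment", which is the end of period 1 (V11). The stated method is "Repeated-measures analysis of covariance (ANCOVA) will be performed to compare the groups, with the baseline K-CRS-R score included as a covariate". The same method is repeated for the secondary outcomes, which include "change in total K-CRS-R score 1 week after the baseline assessment and at the end of the study" and "changes in K-CRS-R subscale scores at 1 week, 2 weeks, and the end of the study compared to the baseline". fMRI and FDG-PET changes from baseline are compared between the groups at each time point by repeated-measures ANOVA, with no covariate named. The EEG sentence specifies repeated-measures ANCOVA with baseline EEG as covariate but does not name the contrast. No treatment, period or sequence effect is mentioned.

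Table 1 schedules K-CRS-R at V2, V11 and V22, and EEG and MRI/fMRI/PET at V2 and V22 only. Sample size estimates gives f of at least 0.25, power 0.80, 22 participants, and 24 enrolled after drop-out.

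**The concern.** A group label that means treatment order coincides with a treatment label only while the first treatment is being given. After the switch, Group B is the more recently treated group, and a comparison of A with B no longer answers whether P-tDCS beats sham. The plan nevertheless lists end-of-study group comparisons of the K-CRS-R total and subscales as secondary outcomes. On Table 1's schedule, the imaging outcomes have no other post-baseline comparison. If the plan is followed as written, a device that works could be reported as having no effect or a harmful one on these outcomes.

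The primary comparison raises a different and milder question: whether a first-period comparison of about 11 patients with 11 has the power that the protocol states.

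**Working it through.** **Inputs from the protocol article.** N = 22 evaluable, 1:1 allocation, f = 0.25, power 0.80, p < 0.05. Primary time point 2 weeks after baseline, as both the Outcomes and the Statistical analyses sections have it.

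**Assumptions, not in the document.** Two-sided test. f = 0.25 read as d = 2f = 0.5 SD. Equal correlation rho between K-CRS-R assessments, varied from 0.3 to 0.8. Carry-over c = fraction of the P-tDCS effect still present at the end of period 2 in Group A.

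**Step 1: the plan's own figure.** The stated inputs do not determine 22, because the test family, the number of measurements m and rho are not given. A within-patient type of test has noncentrality f²·N·m/(1 − rho).
- m = 2, rho = 0.7: 0.0625 × 22 × 2 / 0.3 = 9.17, power 0.82.
- m = 5, rho = 0.5: 0.0625 × 22 × 5 / 0.5 = 13.75, power 0.84.
- m = 2, rho = 0.5: 5.5, power 0.61 (34 patients needed).

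A plain two-group comparison with f = 0.25 has noncentrality 0.0625 × 22 = 1.375 and power 0.20, and needs 128 patients in total. So 22 fits a within-patient type of test and not a comparison of two groups.

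**Step 2: power of the 2-week comparison.** For ANCOVA on first-period data, SE = √[(1 − rho²)·4/N] with N − 3 degrees of freedom. For the cross-over contrast of V11 and V22, SE = √[2(1 − rho)/N] with N − 2 degrees of freedom. At rho = 0.7 these are √(0.51 × 4/22) = 0.305 and √(0.6/22) = 0.165, so d/SE is 1.64 and 3.03.

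| rho | First-period ANCOVA, power | Cross-over contrast, power (c = 0) |
|---|---|---|
| 0.3 | 0.21 | 0.47 |
| 0.5 | 0.25 | 0.61 |
| 0.6 | 0.29 | 0.70 |
| 0.7 | 0.34 | 0.82 |
| 0.8 | 0.46 | 0.94 |

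For 80% power, the first-period ANCOVA needs from 118 patients (rho = 0.3) down to 48 (rho = 0.8).

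**Step 3: what A minus B means at each time.** Let t be the true effect of P-tDCS over sham. Period effects common to both groups cancel.
- V11: A has t and B has 0, so A − B = t.
- V22: A has c·t and B has t, so A − B = (c − 1)·t.
- Cross-over estimate: ½[(V11 − V22 in A) − (V11 − V22 in B)] = ½[(1 − c)t + t] = t(1 − c/2).

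| t = 0.50 SD | A − B at V11 | A − B at V22 | Cross-over estimate |
|---|---|---|---|
| c = 0 | +0.50 | −0.50 | 0.50 |
| c = 0.5 | +0.50 | −0.25 | 0.375 |
| c = 1 | +0.50 | 0 | 0.25 |

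A simulation gave the same values to within 0.01. The result at V22 is algebraic and does not depend on rho or on the size of t.

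**Step 4: cost of carry-over to the cross-over estimate.** At rho = 0.7 its power is 0.82, 0.58 and 0.30 for c = 0, 0.5 and 1, against 0.34 for the first-period ANCOVA, which carry-over does not touch. The gain in precision is gone at full carry-over.

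**The case against.** Several points on the other side stand.

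- The 2-week primary is a legitimate randomised comparison, free of carry-over. The protocol justifies the cross-over by giving every patient access to tDCS, not by precision, and a first-period primary is consistent with that. A reader might infer that the primary analysis is invalid or estimates the wrong quantity. The document does not support this: the shortfall is in power.
- A reader might also infer that the treatment effect is never analysed within patients. That goes too far. The tDCS device section also uses the word groups for the two conditions, the repeated-measures structure is not spelled out, the sample size fits a within-patient type of test, and a group-by-time term would recover the effect. A full analysis plan may say more.
- A pooled group main effect over V11 and V22 has expectation c·t/2, which is zero without carry-over. This arises only if both visits enter one model and no interaction is tested. The primary outcome is set at 2 weeks, so this does not touch it.
- Zero carry-over is itself an assumption. The Introduction cites recovery maintained for up to 1 week after tDCS.

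None of this rescues the end-of-study comparisons. The text names the method, the contrast and the time points, and takes change from the single study baseline. Table 1 has no K-CRS-R after wash-out from which a period-2 change could be formed. This is a stated contrast that does not match the design, not detail left to another document.

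**Conclusion.** The point holds in two parts of unequal weight.

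1. The end-of-study comparisons of Group A with Group B, for the K-CRS-R total and subscales and, on Table 1's schedule, for imaging, do not estimate P-tDCS versus sham. For a working device the difference has the reversed sign without carry-over and is near zero with full carry-over. This follows from the definition of the groups and needs no assumed correlation or effect size. It concerns secondary and exploratory outcomes.

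2. The 2-week primary is valid but inefficient. Its power is about 0.21 to 0.46 with 22 patients, not 0.80, given an effect of 0.5 SD and rho from 0.3 to 0.8. A cross-over estimate would do better if carry-over is small. With rho = 0.7 its advantage disappears at full carry-over.

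For EEG the charge is narrower. The contrast is not named, and Statistical analyses mentions a 2-week EEG that Table 1 does not show. If groups are compared at V22, the same problem applies.

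**What to change.** - Replace the end-of-study group comparisons of K-CRS-R total and subscales with a linear mixed model on the V11 and V22 values. Use treatment received, period, sequence and institution as fixed effects and patient as a random effect, and report the P-tDCS minus sham coefficient.
- Report it beside the period-1-only ANCOVA and name in advance which of the two is primary. If the ANCOVA stays primary, restate the power in Sample size estimates for that test. If the cross-over model becomes primary, state the test family, m and rho, and the carry-over assumed.
- State that end-of-study differences between A and B, including EEG and imaging, will not be interpreted as efficacy. Reconcile the EEG time points in Statistical analyses with Table 1 before applying the model to EEG; with EEG at V2 and V22 only, it cannot be fitted.
- In the tDCS device section, replace the group labels by P-tDCS period and sham period.

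**Cost.** No new patients, and the K-CRS-R scores needed are already scheduled. Recruitment began in May 2022, so a change of primary analysis needs a dated amendment made without sight of unblinded data. The statistical price is attenuation of the cross-over estimate under carry-over, from 0.5 to about 0.375 SD at 50% and 0.25 SD at 100%, which is why the first-period result should stand beside it.

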## Introduction

Acquired brain injury can result in prolonged disorders of consciousness (DOC) including coma, “unresponsive wake syndrome” (UWS; also called vegetative state [*VS*]) (1) and a minimally conscious state (MCS) (2). Several studies have attempted to determine the effectiveness of brain stimulation techniques, such as deep brain stimulation (DBS) (3), transcranial magnetic stimulation (4), and transcranial direct stimulation (tDCS), for improving the level of consciousness of patients with DOC (5). In particular, tDCS therapy is emerging as a non-invasive treatment, with no side effects such as seizures (6).

tDCS is a form of cortical stimulation in which anode and cathode electrodes are attached to the scalp or forehead and continuous direct current is applied. Several studies have reported that anodal stimulation of the damaged cortical area in DOC patients improves the function of the stimulated area. The dorsolateral prefrontal cortex (DLPFC) is the most important target region to improve consciousness in DOC patients. One study showed that a single session of tDCS over the left DLPFC improved the level of consciousness in 43% of patients in an MCS (7) In a study of UWS and MCS patients, tDCS was used to activate the left DLPFC and restore consciousness, and all MCS patients showed immediate clinical improvement after the tDCS intervention. Patients who received a second tDCS treatment 3 months after the first showed additional clinical improvement and the emergence of consciousness (8). In another study, consciousness was restored in chronic MCS patients through repeated tDCS treatment, and a significant change in the Coma Recovery Scale-Revised (CRS-R) score was seen compared with a sham tDCS treatment. Moreover, recovery of consciousness was maintained for up to 1 week after the end of tDCS treatment (9). tDCS has also been applied in clinical settings, as it can easily be customized by varying the position, size, number, and current of electrodes without any major adverse events.

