**Figure 1 fig1:**
[figure not shown]
The study protocol.

**Table 1 tab1:** Study design.

	Screening	Baseline	Period 1		Outcome	Wash-out period	Period 2		End of study
			Session 1	Session 2			Session 1	Session 2	
Visit	V1	V2	V3 ~ V6	V7 ~ V11	V11	2 weeks	V12 ~ V16	V17 ~ V21	V22
ENROLLMENT									
Informed consent	**V**								
Eligibility screen	**V**	**V**							
Randomized allocation		**V**							
Taking a clinical photo	**V**								
MRI-based simulation and planning for tDCS		**V**							
INTERVENTIONS									
Personalized tDCS Sham-tDCS		**V**	**V**	**V**			**V**	**V**	
ASSESSMENTS									
Outcome variables		**V**							
Vital signs	**V**	**V**	**V**	**V**	**V**	**V**	**V**	**V**	**V**
Physical examination	**V**	**V**							
K-CRS-R		**V**			**V**				**V**
EEG		**V**							**V**
NCS-R		**V**	**V**	**V**	**V**	**V**	**V**	**V**	**V**
MRI, fMRI, and PET scan		**V**							**V**
Other variables Adverse events		**V**	**V**	**V**		**V**	**V**	**V**	**V**

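### Table 1 schedules K-CRS-R only at V2, V11 and V22, which contradicts the stated 1-week outcomes and leaves period 2 without a pre-treatment score

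*Protocol article*

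**What the plan says.** - **Schedule.** After screening (V1) and baseline (V2), the visit row of Table 1 runs "V3 ~ V6 V7 ~ V11 V11 2 weeks V12 ~ V16 V17 ~ V21 V22". K-CRS-R is marked in three of the nine columns: V2, V11 and V22. The washout column, both session columns of period 1 and both session columns of period 2 are empty for K-CRS-R.
- **Outcomes.** Primary and secondary outcomes states: "The primary outcome will be the change in total K-CRS-R score 2 weeks after the baseline assessment". The same section lists 1-week and 2-week changes in the total score as secondary. Statistical analyses repeats this ("The first secondary outcome to be evaluated will be the change in total K-CRS-R score 1 week after the baseline assessment") and adds subscale changes at 1 week, 2 weeks and end of study. Each analysis uses one baseline K-CRS-R score as covariate.
- **Abstract.** It places the secondary K-CRS-R assessments one and two weeks after the experimental session, and the primary at the end of the first treatment day.
- **Design.** Enrollment and randomization gives the sequence "Group A: P-tDCS (period 1), washout period (> 2 weeks), and sham tDCS (period 2"; Group B has the reverse order. The tDCS device section adds: "Each tDCS intervention will be performed 10 times over 2 weeks". Table 1 gives the washout as 2 weeks, without the greater-than sign.
- **Background.** The Introduction reports from an earlier study that "recovery of consciousness was maintained for up to 1 week after the end of tDCS treatment".

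**The concern.** There are two separate problems. First, the article defines secondary outcomes at a time when its own schedule takes no measurement. A statistical analysis plan cannot recover scores that were never taken.

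Second, the outcome is a change from baseline, adjusted for baseline, in a cross-over, yet only one pre-treatment score is scheduled. For period 2 the available starting values are V2, about four weeks before V12 (two weeks of treatment plus a washout of at least two), or V11, taken at the end of the first treatment. Neither is an untreated score at the start of period 2. With no K-CRS-R between V11 and V22, the trial cannot show directly that scores returned to their pre-treatment level before the second treatment. If both periods are pooled and some period-1 benefit persists, the sham period that follows P-tDCS looks better than it should, and the estimated effect shrinks.

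**Working it through.** **1. Schedule against outcomes.** The plan gives no figure for this point, so the check is a comparison of the text with Table 1.

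| Needed by the text | K-CRS-R visit required | Marked in Table 1? |
|---|---|---|
| Change at 2 weeks (primary) | V2 and V11 | yes |
| Total and subscales at 1 week | about V6/V7 (and V16/V17 for period 2) | no |
| 1 week after the experimental session (Abstract), period 1 | washout | no |
| End of study | V22 | yes |
| Period-2 pre-treatment score | V12 before stimulation | no |

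Text extraction is an unlikely cause. The K-CRS-R row has all nine cells, and the NCS-R row is filled in every column from baseline on, including washout and period 2. The K-CRS-R assessments required for eligibility precede treatment and fill none of these gaps.

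**2. Outcome lag.** Table 1 marks the intervention at V2, so V2 to V11 are ten sessions and V11 is the day of the tenth. V12 to V21 are also ten sessions, but the period-2 score comes at a separate visit, V22. The V21–V22 interval is not stated.

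**3. Role of the V2 baseline in a pooled analysis.** (V22 − V2) − (V11 − V2) = V22 − V11. The shared baseline cancels from the within-patient contrast.

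**4. Effect of carry-over on that contrast.** Let delta be the true effect, p1 and p2 the period effects, and c the fraction of the period-1 benefit still present at V22.

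- Group A, mean V11 − V22: delta − c·delta + (p1 − p2)
- Group B, mean V11 − V22: −delta + (p1 − p2)
- Half the difference: [delta(1 − c) + delta]/2 = delta × (1 − c/2)

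The period effects cancel. The estimate is 87.5%, 75% and 50% of delta for c = 25%, 50% and 100%.

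**5. Illustrative power.** Taken from Sample size estimates: 22 patients and f = 0.25. Assumed: f = 0.25 read as a 0.5 SD difference between two conditions (f = d/2), a two-sided 0.05 level, and the correlation rho between V11 and V22. The SD of the within-patient difference is √(2(1 − rho)), and the noncentrality is 0.5(1 − c/2)·√22 / √(2(1 − rho)). For example, at rho = 0.7 and c = 0 it is 0.5 × 4.690 / 0.775 = 3.03.

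| rho | c = 0 | c = 50% | c = 100% |
|---|---|---|---|
| 0.5 | 61% | 39% | 20% |
| 0.7 | 82% | 58% | 30% |
| 0.8 | 94% | 75% | 42% |

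**6. Carry-over test that the schedule does allow.** Comparing V11 + V22 totals between sequences estimates (1 + c)delta − delta = c·delta. Without baseline adjustment its standard error is √(2(1 + rho)·(1/11 + 1/11)) SD. At rho = 0.7 that is 0.786, against c·delta = 0.25 SD at c = 50% and 0.5 SD at c = 100%. Power is about 6% and 9%.

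**7. Change from V12 as the period-2 outcome.** Let c12 and c22 be the carry-over fractions at V12 and V22. Using each period's own baseline, the expected estimate is [delta − (c22 − c12)delta + delta]/2 = delta × [1 + (c12 − c22)/2]. It is unbiased only if c12 = c22. If carry-over decays between the visits, it overstates the effect.

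**The case against.** The strongest reply is that the text plans the 1-week assessments and the table merely omits them. Table 1 under-marks other items too: EEG has no mark at V11 although a 2-week EEG outcome is stated, and the same holds for the 2-week fMRI and FDG-PET endpoints. An abridged table in a condensed article is plausible, and Figure 1 could not be seen. This stands as far as it goes. A reader might infer that the 1-week scores are not being collected, but the article shows only that its table and text disagree.

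A reader might also infer that the primary outcome is missing or biased. It is not: V2 and V11 are both scheduled, and the V2-to-V11 change precedes any second treatment. Nor does the cross-over require a period-2 baseline. V11 and V22 can be compared directly, and both common spontaneous recovery and the unequal lag are period effects that the randomised sequence balances when period is in the model.

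Finally, a reader might take carry-over as established. The Introduction's figure, persistence for up to 1 week, is shorter than either washout statement. Its remark on re-treatment after 3 months concerns added gain from a second treatment, not persistence of the first. Carry-over is therefore a possibility that the schedule cannot check well.

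What remains is the contradiction over the 1-week outcomes, the undefined period-2 baseline, and the absence of any K-CRS-R score with which to check the washout directly.

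**Conclusion.** The point holds as an internal contradiction with a design consequence. As printed, Table 1 cannot supply the 1-week total and subscale outcomes under either the main text's timing or the Abstract's. It also leaves period 2 without a pre-treatment score, in a plan whose outcome is a baseline-adjusted change.

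The effect on the treatment estimate is conditional. It arises only if both periods are pooled and some benefit lasts to V22. The factor 1 − c/2 is exact under a simple additive model. The power figures rest on the assumed effect scale, correlation and carry-over fraction, and vary widely with the correlation. The available test on totals would almost never detect carry-over at this sample size.

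Severity: should-fix. Stated secondary outcomes are at risk and the remedy is cheap, but the literal primary outcome is intact.

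**What to change.** - Reconcile Table 1 with the Abstract, Primary and secondary outcomes, and Statistical analyses. Add K-CRS-R at the end of week 1 in each period (for example before stimulation at V7 and V17) and before the first period-2 stimulation at V12. This makes six time points instead of three.
- State which score is the period-2 baseline and keep period in the model. Use change from V12 as a sensitivity analysis, not as an automatic replacement, because of the bias shown in step 7.
- Report V12 minus V2 by sequence as a descriptive washout check.
- Assess K-CRS-R at the same lag after the tenth session in both periods.
- Reconcile the two washout statements: "washout period (> 2 weeks" in the text and 2 weeks in Table 1.

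The cost is a schedule amendment and three short bedside assessments per patient at visits that already take place. Recruitment began in May 2022, so patients already past these visits will lack the added scores unless they were taken in practice. The report should say how many patients this affects.
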